#### 2.4.3. Secondary Assessments

On awakening on Day 7, the participants will be managed by investigators to take part in the different evaluations in the same order at each session (Figure 3). They will be given appetite and sleepiness questionnaires to complete throughout the day. After saliva sample and blood sample collection, they will have an ad libitum breakfast. They will then be allocated to three workshops for metabolic fitness, muscle fatigue, and cognitive performance testing following the same order between sessions. Finally, their energy intake will be measured by ad libitum meals for lunch, afternoon snack, and dinner.

Metabolic fitness

After sitting quietly for 20 min, subjects will perform, to the point of volitional fatigue, a graded exercise test on an electromagnetically braked cycle ergometer with continuous gas collection and heart rate monitoring. After a 2-min warm-up involving unloaded pedaling, athletes will start at 60 W and obese participants at 40 W. The work rate will be stepped up by 15 W every 3 min. If the heart rate is unstable, this stage will be extended for up to 5 min to obtain a heart rate stable to ±5 beats. When the respiratory exchange ratio (RER) is greater than or equal to 1.00—indicating no fat oxidation—the work rate will be stepped up by the same increments at 1-min intervals until volitional fatigue is reached. The VO_2_ peak will be considered to have been reached when the RER is greater than or equal to 1.05, and the subject has achieved his age-predicted maximal heart rate (HRmax: 220—age), according to the methodology validated by Riddell et al. (2008) [51]. All the tests will be performed on a portable cycle ergometer (Monark 828E, Goteborg, Sweden). The O_2_ consumption (VO_2_) and CO_2_ production (VCO_2_) will be measured breath-by-breath through a mask connected to an O_2_ and CO_2_ analyzer (MetaMax 3b, Cortex Biophysik, Leipzig, Germany). Ventilatory parameters will be averaged every minute during the submaximal exercise test and the subsequent 10-min recovery period. Heart rate will be monitored continuously throughout the experiments (Polar RS800cx monitor, Polar, Finland).

Muscle fatigue

Subjects will be placed on a dynamometer equipped with a force sensor. The back and hip of the participants will be attached to the back of the chair with a belt to prevent compensatory movements that might bias the force measurements. The angle formed at the hip will be 40° (0° being the angle in the standing position). The participants’ right leg will be firmly attached above the malleolus, and the force sensor screwed to the leg clip. For the maximal voluntary isometric contraction (MVIC) test, participants will perform MVIC of knee extensors (duration = 3 s, recovery = 60 s) on the dynamometer at randomized angles of 66°, 76°, and 87° (0° = full extension, two tests at each angle) to determine the optimal angle. After a standardized 10-min warm-up period at the optimum angle, participants will then maintain a voluntary (static) isometric contraction of 60% of maximum strength. The exercise will end when subjects are unable to keep the required level of force longer than 3 s despite strong verbal encouragement [52,53]. Fatigue and recovery levels will be assessed immediately with an MVIC after exercise and then at 3, 6, and 15 min after cessation of exercise. Neuromuscular fatigue will be determined from the time of contraction retention. The difficulty of the effort will be assessed during the task using a child and adolescent’s subjective perception scale (CERT). The duration of this evaluation is estimated at 30 min.

Cognitive performance

A complete battery of tests including the Stroop color–word test, trail-making task (TMT), barrage test, California verbal learning test (CVLT), and multiple object tracking (NeuroTracker, CogniSens Athletic Inc., Montreal, Canada) will be used to measure cognitive performance (Table 2).

Ad libitum 24 h energy intake

Food will be offered ad libitum in four meals representing 24 h energy intake. The composition of the buffet meal will conform to the adolescents’ tastes as determined by the food questionnaire filled out at baseline. Top-rated items will be avoided to limit excessive intake that might overwhelm the effect of the trial on food intake. The buffets offered the participants will be the same between adolescents and sessions. Sufficient amounts of food and identical meals will be offered for the three sessions, and participants will be asked to eat until satiated; additional food will be available if desired. Food consumption will be weighed and recorded by investigators. Energy intake and macronutrient and micronutrient composition will then be calculated using a professional computerized nutrient analysis program (Bilnut 4.0 SCDA Nutrisoft software) and Ciqual tables (2017 version).

Subjective appetite sensations

Appetite sensations will be collected throughout the day using visual analog scales (150 mm scales). Adolescents will report their hunger, fullness, desire to eat, and prospective food consumption at 13 regulated times: on awakening; before and immediately after breakfast, lunch, snack, and dinner; and at bed time. The questions will be “How hungry do you feel?”, “How full do you feel?”, “Would you like to eat something?”, and “How much do you think you can eat?”. Adolescents will be asked to respond on a scale from “not at all” to “a lot”. This method has been previously validated [56].

Subjective diurnal sleepiness

The Karolinska sleepiness scale will be used to assess alertness/sleepiness at 13 regulated times throughout the day: on awakening; before and immediately after breakfast, lunch, afternoon snack, and dinner; and at bed time. A nine-point verbally anchored scale ranging from 1 to 9 (“extremely alert”–“extremely sleepy”–“fighting sleep”) will be used. Higher scores indicate higher sleepiness [57].

### 2.5. Data Management

Data will be handled in compliance with French law, and collected and recorded on CRFs. A trained research coordinator will record data in an electronic database. All original records will be archived at trial sites for 15 years.

### 2.6. Statistical Analysis

#### 2.6.1. Sample Size Power

The justification of sample size estimation is based on the comparison of mean differences in sleep efficiency (primary outcome) measured pre- and post-intervention, between the three experimental sessions. Few studies report sufficiently robust information on intra-individual variability. We calculated that, for a type I error at 0.017 (correction due to multiple comparisons), a statistical power equal to 90%, and a coefficient intra-individual correlation of 0.5, 22 subjects per adolescent population recruited, either with obesity or athletes, would be needed to demonstrate an effect size of the order of 0.8. This seems reasonable in view of the work reported in the literature [35]. To take into account lost to follow-up, it was finally agreed to include 24 participants per population.

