#### 2.6.2. Preliminary Analysis

Statistical analyses will be conducted with Stata v15 (StataCorp, College Station, TX, USA). Two-sided p < 0.05 will be considered statistically significant. Participants will be described at baseline and compared between randomized groups in terms of compliance with eligibility criteria, demographic characteristics, clinical characteristics, and treatments. The comparability of groups at baseline will be assessed on the main participant characteristics and potential factors associated with the primary outcome. A possible difference between groups in any of these characteristics will be determined by both clinical and statistical considerations. The number of participants included and the inclusion curve will be presented by group.

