#### 2.6.3. Analyses for Preliminary Endpoint

Intention-to-treat analysis will be considered for the primary analysis. To prevent attrition bias, imputation of missing data is planned. The statistical analysis plan also provides for an additional per-protocol analysis.

To study the effect of quality of protein intake on quality of sleep, the primary analysis will be performed using statistical tests for repeated correlated data. Mixed models to take into account between and within subject variability will be used, considering the following fixed effects: study of protein (PROT-REF, PROT1, and PROT2), point-time evaluation, period, order, and carry-over together with their interactions (including *protein × point-time evaluation*), with subject as a random-effect. Then, the group effect (adolescent rugby players vs. adolescents with obesity) will also be studied, and special attention will be paid to the interaction status *group × proteins*.

These analyses will be followed if necessary (p < 0.05) by a post-hoc test suitable for multiple comparisons such as the Tukey–Kramer test. Multivariable analysis should be used to complete the aforementioned analyses, to take into account possible confounding factors including age and BMI. Results will be expressed in terms of effect sizes and 95% confidence intervals.

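### The 90% power at 22 per population comes from a one-step paired formula, and 2.6.1 does not say which SD and correlation it uses; power for the protein × time contrast is about 53% to 89%, depending on the reading and the model

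*Protocol article*

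**What the plan says.** Section 2.6.1 defines the quantity being powered as the "comparison of mean differences in sleep efficiency (primary outcome) measured pre- and post-intervention, between the three experimental sessions". Its inputs are "for a type I error at 0.017 (correction due to multiple comparisons"), an effect size of the order of 0.8, and "a statistical power equal to 90%, and a coefficient intra-individual correlation of 0.5, 22 subjects per adolescent population recruited". The 22 per population is raised to 24 for loss to follow-up. The same section says that robust information on intra-individual variability is scarce, so the 0.5 is an assumption.

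Section 2.3.2 places the EEG recordings on Night 3 (end of washout) and Night 6 (end of supplementation) of each of three sessions. Section 2.6.3 analyses sleep efficiency with a mixed model that has fixed effects for protein, time point, period, order and carry-over, and their interactions, including protein × time point, "with subject as a random-effect". Section 2.6.2 makes the tests two-sided.

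The article does not say which standard deviation (SD) standardises the 0.8, or which two quantities the 0.5 correlates.

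**The concern.** A comparison of two proteins uses four nights per boy: Night 6 minus Night 3 under one protein, less the same difference under the other. A single paired difference between two nights uses only two. The stated 22 is what the formula for one paired difference gives. That formula fits the four-night contrast only if both inputs already describe the pre-post changes. If they describe single nights, the variance is doubled and the trial is much weaker than stated.

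This is the power claim for the primary endpoint, made separately for each population. The authors and readers will use it to judge how informative a non-significant result is. The answer also depends on whether the analysis model can use the correlation that the calculation relies on.

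**Working it through.** **Inputs.** From 2.6.1: alpha 0.017, power 90%, correlation 0.5, effect 0.8, n = 22 evaluable. Two-sided testing is stated in 2.6.2 and assumed for the sample size. z(1 − 0.017/2) = 2.387 and z(0.90) = 1.282.

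**Step 1. The plan's own figure.** For one paired difference with correlation ρ, the variance is 2(1 − ρ) = 2 × 0.5 = 1 in units of SD².

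n = 2(1 − ρ)(2.387 + 1.282)² / 0.8² = 13.46 / 0.64 = 21.03, rounded up to 22.

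The figure is reproduced. Normal-approximation power at 22 is 91.4%. An exact paired t-test (21 df) has 86.6% at 22 and needs 24 for 90%.

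**Step 2. Reading A: 0.5 is the correlation between any two single nights.** This is the structure that a subject random intercept implies. The four-night contrast has variance 4(1 − 0.5) = 2, so the standardised effect is 0.8/√2 = 0.566. A change has variance 2(1 − 0.5) = 1 here, so the change SD equals the single-night SD and either scale for the 0.8 gives the same result.

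- n for 90%: 13.46 / 0.32 = 42.05, so 43 (normal); 45 (paired t).
- Power at 22: 53.4% (paired t, 21 df), 59.1% (t with about 100 model df, an assumption), 60.5% (normal).
- Power at 24: 58.4%, 63.7% and 65.0% respectively.
- Effect detectable with 90% power at 22: √2 × (2.387 + 1.282)/√22 = 1.11 SD (normal); 1.19 SD (paired t).

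**Step 3. Reading B: 0.8 is in SDs of the change, and 0.5 is the correlation of changes between sessions.** The contrast has variance 2(1 − 0.5) = 1 and Step 1 applies. Power at 22 is 86.6% (paired t on change scores) or 89.2% (pooled change-score analysis, 42 df).

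**Step 4. Reading B analysed with a subject intercept only.** Changes with variance 1 and correlation 0.5 need a residual variance of 0.25 and a subject-by-time variance of 0.25: change variance 2 × 0.25 + 2 × 0.25 = 1, covariance between changes 2 × 0.25 = 0.5. An intercept-only model puts the subject-by-time variation into the residual. Of the five within-subject degrees of freedom, one has variance 0.25 + 3 × 0.25 = 1.0 and four have 0.25, so the pooled residual is (1.0 + 4 × 0.25)/5 = 0.40. The model then takes the contrast variance as 4 × 0.40 = 1.6 when the true value is 1.

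With about 105 df the critical value is 2.425, which on the true scale becomes 2.425 × √1.6 = 3.07. The expected statistic is 0.8 × √22 = 3.75, so power ≈ Φ(3.75 − 3.07) = 75%. A simulation of this case (22 subjects, six nights, complete data, no period or carry-over terms) also gave 75%. The same simulation under Reading A gave 59%.

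**Step 5. Range over the correlation of changes.** Effect 0.8 in change SDs, n = 22, change-score analysis:

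| Correlation of changes between sessions | Normal | Paired t |
|---|---|---|
| 0 | 60.5% | 53.4% |
| 0.25 | 75.1% | 68.0% |
| 0.4 | 85.1% | 78.9% |
| 0.5 | 91.4% | 86.6% |

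If instead 0.8 is in single-night SDs and changes are uncorrelated, normal-approximation power is 60.5%, 71.9%, 85.1% and 91.4% for within-session correlations of 0.5, 0.6, 0.7 and 0.75.

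**The case against.** The strongest reply is that 2.6.1 names the pre-post differences as the quantity compared. The 0.8 and 0.5 can then be read as the effect on those differences and their correlation between sessions, and 22 is reproduced. This stands. A reader might infer that the calculation ignored the pre-post structure, or that 53–61% is simply the power on the plan's own inputs. The text supports neither. The 53–61% needs the further assumption that 0.5 is an equal correlation among all six nights, which the article does not state.

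It is also tempting to say that a subject intercept forces uncorrelated changes, so that Reading B falls back to 53–61%. That confuses the fitted model with the data. If changes truly correlate 0.5, the estimate keeps its smaller variance, and the cost of the intercept-only model is an inflated standard error (Step 4: 75%).

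Section 2.6.3 does not say that the subject effect is the only random effect, or that it is an intercept, and the full covariance structure may be in the statistical analysis plan. This too stands, so the model-based figures are conditional. It does not remove the point, because the article fixes the power, n, effect and correlation itself and leaves the last two undefined.

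Finally, results will be reported with confidence intervals, the Discussion admits the small sample, and the populations will also be pooled. With 44 evaluable, even Reading A gives 0.566 × √44 = 3.75 and normal-approximation power of 91.4%. That softens the consequence, but 2.6.1 sizes each population separately.

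**Conclusion.** The point holds as an undefined and somewhat optimistic power statement. The contrast is a difference of two changes, and 22 is correct for it only under Reading B with a normal approximation. For 22 evaluable per population, two-sided alpha 0.017 and effect 0.8:

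- Reading A: about 53–61%, with about 43–45 per population needed for 90%.
- Reading B, change-score analysis: about 87–89%, a narrow miss. The exact paired t-test needs 24, which leaves no margin for the losses that the two extra boys were meant to cover.
- Reading B, subject intercept only: about 75%.

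With t-based tests, none of the three reaches 90% at 22. Which one applies cannot be settled from the article, so no single figure should replace the 90%. The results assume complete data and, for the model-based figures, that the subject effect in 2.6.3 is a random intercept with no subject-by-time term.

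**What to change.** In 2.6.1, state which SD standardises the 0.8 (single-night or change) and which correlation the 0.5 is (between nights, or between session changes). Then restate the power, or the effect detectable with 90% power, at 22 evaluable per population for the protein × time contrast under the model in 2.6.3. Use a t-based calculation and show the range over plausible correlations, as in Step 5.

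If correlated changes are intended, analyse change scores or add a subject-by-time random effect in 2.6.3, so that the model uses the correlation that the calculation assumes.

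The cost is a rewritten paragraph and perhaps one line on the model. No extra participants are needed. The downside is a less favourable stated power.

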#### 2.6.2. Preliminary Analysis

Statistical analyses will be conducted with Stata v15 (StataCorp, College Station, TX, USA). Two-sided p < 0.05 will be considered statistically significant. Participants will be described at baseline and compared between randomized groups in terms of compliance with eligibility criteria, demographic characteristics, clinical characteristics, and treatments. The comparability of groups at baseline will be assessed on the main participant characteristics and potential factors associated with the primary outcome. A possible difference between groups in any of these characteristics will be determined by both clinical and statistical considerations. The number of participants included and the inclusion curve will be presented by group.

#### 2.6.3. Analyses for Preliminary Endpoint

Intention-to-treat analysis will be considered for the primary analysis. To prevent attrition bias, imputation of missing data is planned. The statistical analysis plan also provides for an additional per-protocol analysis.

To study the effect of quality of protein intake on quality of sleep, the primary analysis will be performed using statistical tests for repeated correlated data. Mixed models to take into account between and within subject variability will be used, considering the following fixed effects: study of protein (PROT-REF, PROT1, and PROT2), point-time evaluation, period, order, and carry-over together with their interactions (including *protein × point-time evaluation*), with subject as a random-effect. Then, the group effect (adolescent rugby players vs. adolescents with obesity) will also be studied, and special attention will be paid to the interaction status *group × proteins*.

These analyses will be followed if necessary (p < 0.05) by a post-hoc test suitable for multiple comparisons such as the Tukey–Kramer test. Multivariable analysis should be used to complete the aforementioned analyses, to take into account possible confounding factors including age and BMI. Results will be expressed in terms of effect sizes and 95% confidence intervals.

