To limit inter-individual differences, participants will undergo a washout period (three days). During this period, their diet will be set to the recommended dietary allowance (RDA) (1.8 × basal metabolism for athletes and 1.3 × basal metabolism for adolescents with obesity) with protein intake fixed at 1.2 g.kg^−1^. The RDA will be calculated individually for each subject. Three meals and a snack will be offered each day. The meal trays will be prepared in advance and will be the same between sessions. At the last night of washout (Night 3), five saliva samples will be collected to capture DLMO (3, 2, and 1 h before bedtime, bedtime, and 1 h after bedtime). Participants will be fitted with the Sleep Profiler-PSG2 TM for the night. On awakening next day, two saliva samples (on awakening and 60 min later) will be taken to measure morning cortisol level, and blood samples will be collected in the fasting state to measure several biochemical markers related to sleep, food intake, metabolism, and inflammation. During the next three days, dietary intake will be supplemented with protein shakes (PROT-REF = 0.04, PROT1 = 0.07, or PROT2 = 0.11). From Day 4 to Day 6, the diet will be iso-energetic to the washout period (Days 1—3) diets. However, protein intake will be raised from 1.2 to 1.6 g.kg^−1^ through (PROT-REF, PROT1, or PROT2) shakes and intake from other macronutrients will be adjusted accordingly. Similar to Night 3, participants will collect five saliva samples and undergo electroencephalogram (EEG) recordings during Night 6.

At Day 7 (Figure 3), on awakening, saliva samples and blood samples will be collected. Food will then be offered ad libitum in four meals (breakfast, lunch, afternoon snack, and dinner) representing 24 h energy intake. Participants will be asked to fill out visual analog scales for their appetite sensations and sleepiness level throughout the day. After breakfast, participants will take part in evaluations including metabolic fitness on submaximal test, muscle fatigue measured by time of maintenance of strength of the knee extensor muscles, and cognitive performance measured by a battery of tests (Stroop, trail marking, trail-making task, barrage test, California verbal learning, and multiple object tracking).

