Venous blood samples will be taken via an indwelling catheter at 07:30 am in the fasting state. Samples will be collected in EDTA K2 Vacutainer^®^ tubes (Becton Dickinson, Franklin Lakes, NJ, USA), Vacutainer^®^ Lithium Heparin tubes (Becton Dickinson, Franklin Lakes, NJ), and in Vacutainer^®^ SST II Advance tubes (Becton Dickinson, Franklin Lakes, NJ, USA). Samples collected will be immediately centrifuged at 3000× *g* for 10 min at 4 °C except for blood samples on SST tubes, which will be centrifuged after 30 min. After centrifugation, the serum aliquots will be frozen and stored at −80 °C until analysis for cytokines; all other blood samples will be analyzed immediately.

Blood samples will be taken at two time points (Days 4 and 7) in each session for the analysis of glucose, cholesterol triglycerides, urea, serum glutamic oxaloacetic transaminase (AST), serum glutamic pyruvic transaminase (ALT), insulin, leptin, ghrelin, adiponectin, GLP-1, PYY-36, nesfatin, irisin, GH, GHRH, TSH, serotonin, kynurenine, CRP, IL-1β, Il-6, TNF-α, IL-4, IL-10, sTNFR1, and sTNFR2. Plasma amino acids will be analyzed. The plasma Trp/LNAAs ratio will be calculated as Trp concentration (in μmol/L) divided by the sum of LNAAs. Changes in all biomarkers will be measured as the differences between Days 4 and 7 of each session.

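### Using each session's Night 3 sleep efficiency as a second response rather than a covariate makes the protein contrast less precise than the recorded nights allow, by an amount that depends on an unstated correlation

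*Protocol article*

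**What the plan says.** Each session has one EEG night at the end of the washout, before any shake, and one at the end of supplementation. Section 2.3.2 says: "Similar to Night 3, participants will collect five saliva samples and undergo electroencephalogram (EEG) recordings during Night 6".

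Section 2.6.1 sizes the trial on the "comparison of mean differences in sleep efficiency (primary outcome) measured pre- and post-intervention, between the three experimental sessions". Its inputs are "for a type I error at 0.017 (correction due to multiple comparisons"), "a statistical power equal to 90"%, "a coefficient intra-individual correlation of 0.5" and an effect size of 0.8. It arrives at 22 boys per population, raised to 24 for losses.

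Section 2.6.3 specifies the primary model with fixed effects "study of protein (PROT-REF, PROT1, and PROT2), point-time evaluation, period, order, and carry-over together with their interactions (including *protein × point-time evaluation") and a random effect for subject. Age and BMI are the adjustment factors it names, and they belong to a complementary multivariable analysis. Night 3 sleep efficiency is not named as a covariate.

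Section 2.6.4 carries the same approach to the secondary endpoints. For blood markers, section 2.4.2 states: "Changes in all biomarkers will be measured as the differences between Days 4 and 7 of each session".

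**The concern.** In a parallel-group trial, subtracting a baseline removes stable differences between people. In this crossover the subject effect has already done that. Subtracting Night 3 then helps only as far as two nights in one session are more alike than two nights in different sessions. Where they are not, each Night 3 recording adds noise to the protein comparison and removes none.

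The interaction contrast fixes the coefficient of the Night 3 difference at 1, whatever the data show. A covariate lets the data set it. The choice matters because the sample is small, which the Discussion lists as a limitation, and because section 2.6.1 concedes that robust information on intra-individual variability is scarce. A real effect of the planned size could be missed with recordings that were able to show it.

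**Working it through.** **Inputs.** From section 2.6.1: alpha 0.017, power 90%, correlation 0.5, effect 0.8, n = 22 (24 enrolled). Two-sided testing is taken from section 2.6.2: "Two-sided p < 0.05 will be considered statistically significant". Not given: r, the SD that scales 0.8, and whether 0.5 correlates single nights or change scores.

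**The plan's own figure.** Paired normal formula: n = 2(1 − 0.5)(z for 0.9915 + z for 0.90)² / 0.8² = (2.387 + 1.282)² / 0.64 = 21.03, rounded up to 22. The figure is reproduced. It takes the between-session contrast to have variance 2(1 − 0.5) = 1. A paired t-test gives 86.6% power at n = 22 and 90.1% at n = 24.

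**Variance of the two contrasts.** Set the single-night variance to 1 and let ρ be the correlation between a boy's nights in different sessions. Let D3 and D6 be his differences between two sessions on Night 3 and Night 6. Each has variance 2(1 − ρ), and their correlation is r.

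- Planned interaction, D6 − D3: 4(1 − ρ)(1 − r).
- Night 3 as covariate, D6 − r·D3: 2(1 − ρ)(1 − r²).
- Planned over adjusted: 2/(1 + r), which exceeds 1 for every r below 1.

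If nights in the same session correlate at ρw, then r = (ρw − ρ)/(1 − ρ). One correlation of 0.5 for all nights, which is what a subject-only random effect implies, gives r = 0.

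**Power.** Noncentral t, n = 22, alpha 0.017 two-sided, noncentrality 0.8√22/SD, df 21 (planned) or 20 (adjusted), no carry-over term. For example, at r = 0 on the single-night scale the noncentrality is 3.75/√2 = 2.65 planned and 3.75 adjusted. On the change-score reading the planned variance is 1 and the adjusted variance is (1 + r)/2.

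| r | Single-night: planned | adjusted | loss | Change-score: planned | adjusted | loss | CI width ratio, √(2/(1+r)) |
|---|---|---|---|---|---|---|---|
| 0 | 53.4% | 86.3% | 33 | 86.6% | 99.4% | 13 | 1.41 |
| 0.3 | 71.5% | 89.6% | 18 | 86.6% | 97.3% | 11 | 1.24 |
| 0.5 | 86.6% | 94.8% | 8 | 86.6% | 94.8% | 8 | 1.15 |
| 0.7 | 98.3% | 99.3% | 1 | 86.6% | 91.7% | 5 | 1.08 |

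The loss columns are in percentage points. At n = 24 and r = 0 the single-night figures are 58.4% and 89.9%.

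**Simulation.** A three-period crossover with six sequences (an assumption; the article does not list the sequences), with subject and period effects fitted and n = 22, gave 57% against 88% at r = 0, 74% against 90% at r = 0.3, and 89% against 96% at r = 0.5. Mean estimates lay between 0.795 and 0.806 for a true 0.8. Type I error was 0.014 to 0.021 against a nominal 0.017. Neither estimator showed bias.

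**Carry-over term.** Both models keep it. In the six-sequence design, first-order carry-over multiplies the variance of either protein contrast by 1.25. At n = 22, r = 0, single-night scale, power becomes about 43% planned against 77% adjusted. Both absolute figures fall, but the gap remains.

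**The case against.** **The size is uncertain.** The sizing text speaks of pre-to-post differences, so 0.8 and 0.5 may well describe change scores. The planned contrast then meets its target (87% at n = 22, 90% at n = 24, paired t) and the loss is moderate. This objection stands as to size. It sits awkwardly with a subject-only random effect, which implies no correlation between change scores of different sessions, but the article does not settle the matter.

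**Nights in one controlled week may be more alike than nights in different weeks.** That would make r positive and shrink the loss, to about 1 point at r = 0.7 on the single-night reading. This stands too.

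**Stronger readings that the document does not support.** A reader might infer that the plan simply forfeits some 30 points of power. That needs both r = 0 and single-night scaling. A reader might also infer that the loss stays that large whatever r is, because fitting only a subject intercept leaves session variation in the error term. Simulation of that literal model does show a persistent loss. But it treats one clause in a condensed article as the complete covariance structure, and that detail may lie in the full analysis plan. Nor is the analysis biased or invalid: it estimates the pre-to-post change on which the trial was sized.

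**Other routes in the plan.** The list of confounders is open-ended, and the post-hoc comparisons could include proteins at Night 6. Neither makes Night 3 a covariate in the primary model, and a non-significant interaction could stop the post-hoc step from being reached.

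**Carry-over.** Sessions run in consecutive weeks with a three-day washout. A shift from the previous protein that persists equally to both nights cancels fully in a change score and only partly under covariate adjustment. This is a genuine cost of the alternative.

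**Conclusion.** The concern holds as a point of efficiency. The contrast in section 2.6.3 has 2/(1 + r) times the variance of the Night 3-adjusted contrast, so its confidence intervals are up to 41% wider, at r = 0. In power at n = 22, the avoidable loss is between about 1 and 33 points if 0.8 is in single-night SDs, and between about 5 and 13 points if 0.8 and 0.5 refer to change scores, for r from 0.7 down to 0. The top of the range is the value implied by a single correlation of 0.5 with subject as the only random effect; it is not an established property of the data. The figures rest on alpha 0.017 per comparison, two-sided testing, equal variances on the two nights and no carry-over term. The change is worth making because it costs little and removes the dependence on a favourable, unknown r.

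**What to change.** In section 2.6.3:

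- Make Night 6 sleep efficiency the response of the primary mixed model.
- Keep protein, period, order, carry-over and the random subject effect.
- Replace time point and protein by time point with two Night 3 covariates: the boy's mean Night 3 value over his sessions, and the session's deviation from that mean. The split stops between-boy differences from distorting the within-boy slope.
- Read the protein effect as the adjusted Night 6 difference.
- Keep the Night 3 to Night 6 change as a sensitivity analysis.

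Use the same form for secondary outcomes and biomarkers that have a pre value in each session. State in section 2.6.1 which SD scales 0.8 and what the 0.5 correlates.

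The cost is wording only, with no new data, visits or participants. The model spends one within-boy and one between-boy degree of freedom. It cancels only part of any carry-over that persists equally to both nights; the carry-over term and the change-score sensitivity analysis address this. Sessions without a usable Night 3 recording would rely on the imputation already planned.
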